#### **8.4 Withdrawal of individual subjects**

Subjects can leave the study at any time for any reason if they wish to do so without any consequences. The investigator can decide to withdraw a subject from the study for medical reasons.

##### **8.4.1 Specific criteria for withdrawal**

- Evidence of pregnancy
- Occurrence of serious adverse events
- Lack of efficacy at 12 weeks, defined as no improvement assessed by the PGA (at least 1 step improvement is necessary to continue treatment after 12 weeks)
- Use of prohibited concomitant therapy, or a need for their use
- The need for more than 3 courses of rescue medication
- Anaphylactic reaction or other severe systemic reaction to study drug intake
- Diagnosis of malignancy during study, excluding non-metastatic cutaneous squamous cell or basal cell carcinoma and/or localized carcinoma in situ of the cervix
- Any infection that is opportunistic and other infections whose nature or course may suggest an immunocompromised status
- Administration of a living vaccine
- Severe laboratory abnormalities including:
  - ALAT and/or ASAT values > 300% of the upper limit of normal
  - Lowered full blood count indicating a possible (developing) myelosuppression (to be determined by investigator or treating physician)
  - Triglycerides > 9 mmol/l
- Intercurrent severe illness or major surgery
- Protocol violations or if the requirements of the protocol are not respected
- Patient lost to follow up

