#### **8.5 Replacement of individual subjects after withdrawal**

Subjects will not be replaced after withdrawal.

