### **8.6 Follow-up of subjects withdrawn from treatment**

Subjects withdrawn from treatment will continue to be treated at our center, outside the study. All efforts will be made to report the observations for the reason(s) for premature withdrawal and the time of occurrence. If an adverse event is the reason for withdrawal, the physicians of our department will administer therapy as clinically indicated. All serious adverse events and those adverse events for which the relationship to the study drug is plausibly related will be followed up until they have returned to baseline status or stabilized.

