## 10. STATISTICAL ANALYSIS

This trial is designed to demonstrate a superior response to azathioprine compared to alitretinoin in the treatment of severe chronic non-hyperkeratotic hand eczema. Response to treatment is defined as an improvement of  $\geq 2$  steps on the Physician Global Assessment (PGA) developed by Ruzicka et al (8,9) at 24 weeks of treatment.

All analysis will be based on the intention-to-treat principle to guard against attrition bias. Subjects might not only withdraw because the study drug works insufficient, they might also withdraw when their hand eczema is cured.

Missing values will be handled in a way that is dependent on assumptions about the missing data. If the extent and pattern of missing data is known (e.g. missing at random (MAR), missing completely at random (MCAR), missing not at random (MNAR)), an analysis will be chosen that is valid under a plausible assumption about the missing data (probably mixed models). This is according to a strategy proposed by White et al. (28)

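### Withdrawal for any protocol violation (8.4.1), with no week-24 PGA provided for afterwards (8.6), loses outcomes that the intention-to-treat analysis in section 10 needs

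*Protocol*

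**What the plan says.** Four parts of the protocol bear on this.

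- **Section 8.4.1** lists specific criteria for withdrawal. One is "Protocol violations or if the requirements of the protocol are not respected". It has no threshold for severity and no link to safety. Other criteria also depend on how the patient behaves or fares: "Use of prohibited concomitant therapy, or a need for their use"; a need for more than 3 courses of rescue medication; and lack of efficacy at week 12, where "at least 1 step improvement is necessary to continue treatment after 12 weeks".
- **Section 8.4** describes withdrawal as being from the study: "The investigator can decide to withdraw a subject from the study for medical reasons".
- **Sections 8.5 and 8.6** cover what follows. "Subjects will not be replaced after withdrawal". "Subjects withdrawn from treatment will continue to be treated at our center, outside the study". Section 8.6 then provides for recording the reason and time of withdrawal and for following certain adverse events. It does not mention efficacy assessment.
- **Section 10** states: "All analysis will be based on the intention-to-treat principle to guard against attrition bias". For missing values it says that "an analysis will be chosen that is valid under a plausible assumption about the missing data (probably mixed models"). Section 10.1 names a chi-square or Fisher's exact test on the proportions responding at week 24.

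**The concern.** The conduct rules create missing primary outcomes that the analysis principle is meant to protect against. A patient withdrawn under 8.4.1 is managed outside the study, so no week-24 PGA is planned, even though the same clinic continues to see the patient.

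This missingness is unlikely to be neutral. It is triggered by what happens after randomisation, in a trial where patient and treating physician know the allocation (8.2). Using more topical steroid than 5.2 allows may well go with poor response. The opportunity to break a rule also differs by arm. Azathioprine is taken twice daily, with laboratory checks at weeks 1 and 2 and a four-week wait before treatment; alitretinoin is taken once daily without these. The arm-specific prohibited drugs differ too.

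At stake is whether the week-24 response comparison reflects the groups as randomised. An analysis plan can choose how to handle a missing outcome, but it cannot recover an assessment that was never made.

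**Working it through.** **1. The passages side by side**

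| Question | Where | Answer |
|---|---|---|
| Does a violation lead to withdrawal? | 8.4.1 | Yes, any violation |
| What follows withdrawal? | 8.6 | Care outside the study; reason, time and certain adverse events recorded |
| Is a week-24 PGA provided for? | 8.6 | No |
| Who is analysed? | 10 | All, by intention-to-treat, with a missing-data method to be chosen |

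The week-24 response of a withdrawn patient is therefore needed but not observed.

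**2. The plan's own sample size (4.4)**

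Inputs: 33% v 60%, two-sided 0.05, 80% power, 1:1 allocation, drop-out of at most 10%. The pooled two-proportion formula without continuity correction gives 53 per arm, and power at 52 per arm is 0.797. Then 52/0.9 = 57.8, so 58 per arm and 116 in total. The figure reproduces. The inflation treats drop-outs as giving no outcome.

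**3. Hypothetical: no true difference, complete-case test**

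The protocol gives no violation rate, so every input here is assumed. Let p = 0.45 be the true response in both arms, v the share removed, and f the response of those removed relative to those kept. The rate among those kept is p/[(1 − v) + v·f], with 58(1 − v) patients kept.

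| Removed, arm A v arm B | f | Rates among those kept | Difference | Two-sided error |
|---|---|---|---|---|
| 5% v 15% | 0 | 0.45/0.95 = 47.4% v 0.45/0.85 = 52.9% | 5.6 points | about 9% |
| 5% v 15% | 0.5 | 0.45/0.975 = 46.2% v 0.45/0.925 = 48.6% | 2.5 points | about 6% |
| 10% v 10% | 0 | 0.45/0.90 = 50.0% in both | 0 | nominal |

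For the first row, 55.1 and 49.3 patients are kept. The standard error is √(0.474·0.526/55.1 + 0.529·0.471/49.3) = 0.098, and 0.0557/0.098 = 0.57. The rejection probability is Φ(−1.96 + 0.57) + Φ(−1.96 − 0.57) ≈ 0.088. For the second row, 0.025/0.098 = 0.255, which gives about 0.058.

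**4. Hypothetical: the planned effect, under two ways of counting withdrawn patients**

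Assume 33% and 60% among those kept, so a complete-case test sees 27 points. Counting withdrawn patients as non-responders among all 58 per arm gives:

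| Withdrawn, alitretinoin / azathioprine | Rates | Difference | Power | Complete-case power |
|---|---|---|---|---|
| 10% / 10% | 29.7% v 54.0% | 24.3 points | 0.76 | 0.80 |
| 5% / 15% | 31.35% v 51.0% | 19.65 points | 0.58 | 0.80 |
| 15% / 5% | 28.05% v 57.0% | 28.95 points | 0.89 | 0.80 |

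At these assumed rates, the treatment of unobserved outcomes alone moves the estimate by several points.

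**The case against.** The strongest reply is that section 10 already deals with this. It applies intention-to-treat to all analyses, expects withdrawals and foresees a missing-data method. How a withdrawn patient counts in a binary endpoint is commonly left to the analysis plan, which is not shown. This reply stands against several stronger readings that a reader might infer:

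- **That the primary comparison becomes one of adherent patients only.** No section removes withdrawn patients from the analysis. The comparison comes close to that only if they are dropped from the test, or if their outcome is filled in from patients who stayed.
- **That 8.4.1 and section 10 set opposite follow-up rules.** Section 10 sets an analysis principle, not a follow-up rule. What remains is a loss of data that works against its stated aim.
- **That 8.4 permits withdrawal for medical reasons only.** The sentence says what the investigator can decide and does not say that nothing else qualifies; 8.4.1 adds further criteria.
- **That the unblinded treating physician decides.** Section 8.4.1 does not say who applies the criterion.
- **That power necessarily falls below plan.** If violators fall within the 10% allowed in 4.4, about 52 per arm remain and power is about 80%. It would fall to about 75% only if total losses reached 20%, leaving about 46 per arm.

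It can also be said that 8.6 does not forbid a later PGA, and that Tables 1 and 2 list a premature withdrawal assessment. Its content is not described, so it cannot be relied on to supply a week-24 PGA. Nor is the issue confined to violations: the other behaviour- and outcome-dependent criteria lose outcomes in the same way, so deleting one line would not be enough.

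The reply does not remove the core point. A missing-data method rests on assumptions that cannot be checked, whereas these outcomes could be observed.

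**Conclusion.** The concern holds in this form: 8.4.1 and 8.6 together leave the week-24 PGA uncollected for patients withdrawn because of post-randomisation behaviour or course, and this undercuts the purpose that section 10 gives for intention-to-treat.

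The size and direction of any bias are unknown. The spurious difference of about 6 points with 9% error needs three assumptions at once: a complete-case test, a 10-point imbalance in removal, and no response among those removed. With half the response among those removed, it shrinks to about 2.5 points and 6%. With equal removal and equal response among those removed, there is no between-arm bias under the null. None of these figures is a prediction for this trial. The sample-size arithmetic in 4.4 is not in question.

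**What to change.** Reconcile 8.4.1 and 8.6 with section 10 by separating stopping study treatment from leaving the study.

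- In 8.4.1, record protocol violations as deviations and not as a reason to end outcome assessment.
- In 8.6, add that every randomised patient who still consents, whatever the reason treatment stopped, has the scheduled blinded PGA through week 24 and is analysed in the randomised arm.
- If an adherent population is of interest, report a per-protocol analysis as secondary.

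Whether treatment continues after a given event stays a clinical decision, which this change does not prescribe.

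The cost is a few lines of text and a few more study assessments at a clinic the patients already attend. The estimate will include non-adherent patients and may be slightly diluted.

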#### **8.5 Replacement of individual subjects after withdrawal**

Subjects will not be replaced after withdrawal.

### **8.6 Follow-up of subjects withdrawn from treatment**

Subjects withdrawn from treatment will continue to be treated at our center, outside the study. All efforts will be made to report the observations for the reason(s) for premature withdrawal and the time of occurrence. If an adverse event is the reason for withdrawal, the physicians of our department will administer therapy as clinically indicated. All serious adverse events and those adverse events for which the relationship to the study drug is plausibly related will be followed up until they have returned to baseline status or stabilized.

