##### *Patient rated outcome measures (PROMs)*

##### *Quality of life*

- Between-group mean change in quality of life between baseline and 12 and 24 weeks, assessed by the Quality Of Life in Hand Eczema Questionnaire (QOLHEQ). The QOLHEQ is a multi domain disease specific instrument for

hand eczema assessing impairments in quality of life. The score ranges from 0-120, with 120 indicating worst quality of life.

*Patient reported improvement*

- Between-group difference in patients reporting improvement as 'clear or almost clear' at week 12 and 24, assessed by Patient Global Assessment (PaGA). The PaGA takes signs and symptoms into account. It covers 6 degrees of improvement: 'clear or almost clear' (at least 90% clearing of disease signs and symptoms compared to baseline), 'marked improvement' (at least 75% clearing), 'moderate improvement' (at least 50% clearing), 'mild improvement' (at least 25% clearing), 'no change', or 'worsening'. (9)

*Safety and tolerability*

- Adverse events in both groups will be registered.

*Cost-utility and cost-effectiveness*

- Between-group difference in mean Quality Adjusted Life Years (QALY's) will be measured by the EQ-5D-5L score at baseline, week 12 and week 24. The EQ-5D-5L is a measure for HRQoL and utility values. The EQ-5D-5L questionnaire includes a descriptive system, which comprises 5 dimensions of health: mobility, self-care, usual activities, pain/discomfort, and anxiety/depression. Moreover it includes a visual analog scale (VAS), which records the respondent's self-rated health status on a graduated (0–100) scale.
- Direct medical costs will be determined using standardized prices for consultation, treatment (medication; alitretinoin or azathioprine, topical treatment of corticosteroids and emollientia; if necessary oral or topical treatment of antibiotics), diagnostic tests, laboratory measurements, visits to the general practitioner for hand eczema and hospital admissions (in patient and/or daycare). Included patients will be asked to keep track of how much they spend on over-the-counter medication and other products for their hand eczema (out-of-pocket costs). Direct non-medical costs, consisting of travel costs, will be determined using average travel costs to the hospital as determined by relevant Dutch guidelines on cost-studies in healthcare. (22)

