Patients will be given one week to consider participation. Due to this, one extra visit is needed to randomize the patient and obtain baseline data. A Patient Global Assessment (PaGA) one-item questionnaire will be obtained at week 12 and 24. This procedure is only extra in terms of obtaining a quantitative assessment of the qualitative report that a patient provides us in daily practice.

Patients will be asked to keep track of out-of-pocket costs on products for their hand eczema. During each visit, patients will be asked for direct and indirect medical and non-medical costs (see paragraph 8.1.2).

No diagnostic procedures or other treatments will be postponed for patients participating in this study. However, patients receive at least 1 week time to consider participation in the study.

Study overview:

In table 1 and 2 a systematic overview of the study for respectively the alitretinoin and azathioprine arm is presented.

**Table 1.** Study schedule – *alitretinoin* arm

| Visit                                                           | V-1
Screening | V0
Baseline Ali | V1 | V2 | V3 | V4 |
|-----------------------------------------------------------------|------------------|--------------------|----|----|----|----|
| Week                                                            | -1               | 0                  | 4  | 8  | 12 | 24 |
| Screening/baseline                                       |                  |                    |    |    |    |    |
| Check for clinical eligibility (inclusion/exclusion)            | x                |                    |    |    |    |    |
| Sign informed consent                                           |                  | x                  |    |    |    |    |
| Randomization                                                   |                  | x                  |    |    |    |    |
| Baseline data / demographics / medical history / baseline costs |                  | x                  |    |    |    |    |
| Laboratory exclusion criteria post randomization                |                  | x                  |    |    |    |    |
| Start medication                                                |                  | x                  |    |    |    |    |
| Treatment                                                |                  |                    |    |    |    |    |

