- For each group (alitretinoin and cyclosporine), the mean EQ-5D scores overall and of each dimension will be reported. Results from the descriptive system of the EQ-5D-5L will be converted to a utility index value, a population based (social) value specific for the Netherlands. With this value, Dutch utility values will be calculated in order to determine the quality adjusted life years (QALYs) over the study period. Mean values of the EQ-VAS will be reported with a 95% confidence interval. For comparison of means, the Student's t-test or Mann-Whitney U-test will be used, depending on distribution of data.
- The incremental cost-effectiveness ratio (ICER) will be calculated and reported as €/QALY. Effect will be assessed with the PGA. Costs will be assessed as described in paragraph 8.2.

- A regression model will be used to estimate the association between QALYs and the PGA.

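### The protocol does not provide for costs or EQ-5D-5L after withdrawal from treatment, so the 24-week QALYs and ICER are not assured to be intention-to-treat estimates

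*Protocol*

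**What the plan says.** **After withdrawal.** Section 8.6 states: "Subjects withdrawn from treatment will continue to be treated at our center, outside the study". It then provides for two kinds of data. On withdrawal itself: "All efforts will be made to report the observations for the reason(s) for premature withdrawal and the time of occurrence". On safety, serious adverse events and plausibly related adverse events "will be followed up until they have returned to baseline status or stabilized". It mentions neither costs nor questionnaires.

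**How the economic data are collected.** Section 8.3: "During each visit, patients will be asked for direct and indirect medical and non-medical costs". Section 8.1.2 says that QALYs "will be measured by the EQ-5D-5L score at baseline, week 12 and week 24". Tables 1 and 2 place both items at scheduled visits only. They also carry a row for assessing premature withdrawal, under Safety, with no stated content.

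**Which costs count.** The treatment item in the direct medical costs of 8.1.2 reads: "medication; alitretinoin or azathioprine, topical treatment of corticosteroids and emollientia; if necessary oral or topical treatment of antibiotics". Consultations, tests, general practitioner visits and admissions are listed as well. UV therapy and other systemic drugs are not.

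**What triggers withdrawal.** Under 8.4.1, "at least 1 step improvement is necessary to continue treatment after 12 weeks". Using, or needing, a prohibited concomitant therapy is also a criterion, and 5.2 places other anti-eczema systemic treatment and phototherapy among the prohibited therapies.

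**What is promised.** Section 10 puts every analysis on an intention-to-treat footing. Section 10.2 converts EQ-5D-5L to utilities "in order to determine the quality adjusted life years (QALYs) over the study period" and reports an ICER in euros per QALY. Section 2 lists cost-utility and cost-effectiveness among the secondary objectives.

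**The concern.** A 24-week intention-to-treat ICER needs costs and utilities to week 24 for every randomised patient, whatever treatment that patient ends up on. The protocol ties these data to study visits and makes no provision for them once a patient is withdrawn.

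The loss is not random. A patient who does not improve by week 12, or who needs a next-line systemic drug or phototherapy, must be withdrawn, and later care then falls outside the study. The part of the cost that reflects treatment failure is therefore the part least likely to be recorded.

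This cannot be left to a statistical analysis plan. Such a plan can choose a missing-data model, but it cannot recover costs and utilities that were never collected. Nor does counting a withdrawn patient as a PGA non-responder supply them.

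**Working it through.** **1. Planning inputs.** The protocol gives no figure for the economic analysis, no unit prices and no expected week-12 withdrawal rate. The usable inputs are in 4.4: response 33% on alitretinoin and 60% on azathioprine, and drop-out of at most 10%. They are consistent with the stated sample size. The standard two-proportion formula (two-sided 0.05, 80% power, no continuity correction) gives 53 per arm against 52 stated, and power at 52 is 79.7%. Then 52/0.9 = 57.8, so 58 per arm and 116 in total.

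**2. Share of the horizon unobserved.** If a share w of an arm is withdrawn at week t and nothing is collected afterwards, the unobserved share is w × (24 − t)/24.

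- One patient withdrawn at week 12: 12/24 = 50% of that patient's horizon.
- w = 10% (the drop-out ceiling in 4.4): 5% of the arm's horizon if all leave at week 12, and 10% × 20/24 = 8.3% if all leave at week 4.
- w = 20%, 30%, 40% at week 12 (assumed): 10%, 15%, 20%.

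Patients withdrawn under the week-12 rule still supply costs and EQ-5D-5L up to week 12. Patients withdrawn earlier have only a baseline EQ-5D-5L, so their QALYs would rest wholly on modelling.

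**3. Difference between arms.** Planned week-24 non-response is 67% on alitretinoin and 40% on azathioprine. Let a fraction f of these patients leave at week 12. This is assumed; f = 100% is an upper bound, because the week-12 rule requires only one step of improvement and the endpoint requires two.

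| f | Withdrawn, alitretinoin / azathioprine | Horizon unobserved | Extra unobserved weeks per randomised alitretinoin patient |
|---|---|---|---|
| 25% | 16.75% / 10% | 8.4% / 5.0% | 12 × 0.0675 = 0.8 |
| 50% | 33.5% / 20% | 16.8% / 10.0% | 12 × 0.135 = 1.6 |
| 100% | 67% / 40% | 33.5% / 20.0% | 12 × 0.27 = 3.2 |

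**4. Direction of the bias in the cost difference.** Illustrative weekly drug costs (assumed): alitretinoin 1, azathioprine 0.05, next-line treatment c between 0.05 and 2. Take f = 50%. All results are alitretinoin minus azathioprine, per randomised patient.

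- Summing observed costs only: (24 × 0.665 + 12 × 0.335) − 0.05 × (24 × 0.80 + 12 × 0.20) = 19.98 − 1.08 = 18.90.
- With next-line costs included: 18.90 + 12c × (0.335 − 0.20) = 18.90 + 1.62c, which is 18.98 at c = 0.05 and 22.14 at c = 2.
- Letting completers stand in for withdrawn patients: 24 − 24 × 0.05 = 22.80.

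Summing what was observed understates the difference. Filling from completers overstates it over this price range, because withdrawn patients are charged a study drug they no longer take. The two fillings err in opposite directions. Completer filling would equal the result with next-line costs only at c = (22.80 − 18.90)/1.62 = 2.4. Which error applies, and how large it is, depends on data the protocol does not provide for.

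**5. After the fix.** With collection to week 24 regardless of treatment status, the share lost through withdrawal from treatment falls to zero, apart from withdrawn consent and true loss to follow-up. The sample size is unaffected.

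**The case against.** The strongest reply is that 8.6 places the patient's *treatment* outside the study and does not say that measurement ends. Its heading concerns withdrawal from treatment, whereas 8.4 separately covers subjects who leave the study. The premature-withdrawal row in Tables 1 and 2 might include economic data. This stands in part: that collection stops is an inference, and no sentence says so. But no sentence provides for it to continue either, and 8.6 lists what is kept without naming costs or EQ-5D-5L.

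A second reply is that section 10 allows model-based handling of missing values, with mixed models named as likely. That rules out assuming that unobserved costs will simply be counted as zero. It does not close the gap. If no patient is observed after withdrawal, a model can only project from patients still on study drug, which is not what an intention-to-treat cost comparison asks for.

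A third reply is that the general cost question in 8.3 could capture a next-line drug, and that 8.1.2 already names both study drugs, so a switch to the other one could be costed. That is fair as far as it goes, but the question is asked at study visits. The main gap is collection; the incomplete cost list is secondary.

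Finally, 4.4 expects at most 10% drop-out, which would keep the loss near 5% of the horizon. However, 4.4 attributes drop-out to laboratory exclusions and mainly to subjective side effects, and does not mention withdrawals under the week-12 efficacy rule. A higher figure is possible but remains an assumption.

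**Conclusion.** The point holds as a gap in data collection. Followed as written, the protocol does not assure the 24-week intention-to-treat QALYs and ICER that it promises, and the missing part depends on outcome. The loss is 50% of the horizon for each week-12 withdrawal: 5% of an arm's horizon at 10% withdrawn, and 10% to 20% at an assumed 20% to 40%. On the planned response rates it would probably be larger in the alitretinoin arm. The primary analysis of PGA response is a separate matter, and the sample size is not affected.

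Four stronger readings are tempting but not supported.

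- A reader might infer that the arm with more early failures will look cheaper. That follows only if unobserved costs count as zero; filling from completers can reverse it.
- A reader might infer that the sign of the ICER could change. In the illustration above alitretinoin stays dearer throughout, and the document gives no basis for a QALY calculation.
- A reader might picture mainly azathioprine failures moving to alitretinoin. The planned non-response of 67% against 40% points to more failures on alitretinoin.
- A reader might think the financial argument in 11.4 is undermined. That argument rests on drug price given superior efficacy, not on the ICER.

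**What to change.** - In 8.6, state that patients withdrawn from treatment who do not withdraw consent still complete the week-12 and week-24 EQ-5D-5L and the cost assessment, by questionnaire or telephone, including any successor treatment.
- In the direct medical costs of 8.1.2, add other systemic or UV treatment for hand eczema.
- In 10.2, state that all costs and QALYs to week 24 are analysed by randomised arm, whatever treatment was received.

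This is a cheap improvement. The questionnaires exist and the patients remain at the same clinic. The cost is protocol and consent wording, plus one or two extra questionnaires or calls per withdrawn patient. No dose, withdrawal criterion or other clinical rule changes.
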